## Methods

### Study setting

The study will be run in schools in London, Cambridge and surrounding areas, and at the UCL Institute of Cognitive Neuroscience, UK.

^44^. The procedures are uploaded to the trial registration page as a time-stamped private document and will be made available online upon study completion. Following the final participant’s follow-up assessment (one year after the second testing session, T2), all participants will receive an email describing the study purpose and giving them access to all training tasks for 12 months.

### Training procedure and timeline

Participants complete a pre-training assessment, followed by 14 days of training within a four-week period. The training will be completed individually by the participants on their own devices (any device that supports mobile apps). Within one week of the end of the four-week period, participants will complete the post-training assessment. Any deviations from the per protocol timeline due to the constraints of school-based testing will be accounted for in our analyses (see
*Statistical analyses* section). Thirty days after the post-training assessment, participants will be asked to complete an online follow-up assessment. A final follow-up assessment will be completed one year after the post-training session. For a schematic overview of the study timeline see
Figure 1.

**Figure 1. f1:**

Study timeline. T1 – T4 = Assessment time point 1 – 4; A/B/C = refers to the three different versions of the training tasks available in both training groups; Pre- and post-training assessment = Assessment sessions run prior to and after completing the training phase; Training phase = period of training on the app; 1-month and 1-year online follow up assessment = key outcomes will be assessed online one month and one year following the completion of the training.

***Training phase.*** During the training phase, participants from both training groups will be presented with three different training tasks (see below for descriptions). On the first three days they will complete a different version of the training task each day. The presentation order of the three versions will be fixed for days 1–3. The P-Training group will complete the shapes (A), words (B), and faces (C) versions on the first, second, and third day of training, respectively. The AffeCT group will complete the visuospatial (A), auditory (B), and dual (i.e., including both modalities; C) versions of the training task on the first three days of training. From the fourth day of training onward participants in both groups will be free to select any of the three different versions of their training schedule.

At the beginning of the training, both groups will be told that they should spend as much time as possible training on version C due to its benefits to attention, memory and emotion regulation. Version C in the AffeCT will be significantly more cognitively demanding
^45^ than A and B, whereas there are no differences in cognitive demands between versions A, B or C in the P-Training. Emulating the design of established measures of academic diligence and self-regulation
^46–
48^, the ratio of time spent training on version C relative to A and B will be taken as a behavioural index of self-regulation.

***Procedure on each training day.*** On each training day tasks will be populated with a different set of stimuli. In both training groups participants will be given the option to end the training any time from 10 mins onward. The full training session will take between 20–30 mins depending on the level achieved. There will be no limit on the number of training sessions they can complete during a day. Training sessions that are less than 10 mins will not be considered as full training sessions, and will not be included in the analyses, nor will participants be compensated for these sessions.

Each time they start the training, participants will be asked four brief questions about their mood, affect regulatory intentions, social context and current activity. To assess current mood, participants will be asked, “How happy do you feel right now?”. They will provide their mood rating by moving the cursor on a visual analogue scale ranging from “Very unhappy” to “Very happy”. Affect regulatory intentions will be assessed with the question, “Are you trying to change the way you feel right now?”. They will be offered nine answer options from a dropdown menu. Participants will be able to select “No.” or “Yes, by …” followed by different types of regulatory strategies (i.e., distraction, problem-solving, behavioural activation, reappraisal, avoidance, social support, acceptance or other). Social context will be assessed by selecting from a dropdown menu to indicate whether right now they are: “Alone”, “With others (friends/family)”, or “With others (strangers).” Finally, participants will indicate their current activity from a selection of eleven options on a dropdown menu (e.g., commuting, school/work).

***Adherence/retention.*** Participants will be compensated for each section of the study to incentivise enrolment and study completion. They will be paid £10 for each pre- and post-training assessments (T1 & T2) and £5 for both the online follow-up assessments (T3 & T4). Participants will additionally receive £2 per completed training day. If participants complete two or more sessions on a single day they will be paid £5.

*Training.* In addition to payments, retention will be optimised by sending participants a daily training reminder at 8am. Participants who have not completed at least 10 mins of training by 5pm will be sent an additional reminder, informing them that they have a training session waiting for them. A final reminder will be sent at 8pm for any participants who have not completed their minimum training requirement by then.

*Follow-up.* Two weeks after the initial request to complete the follow-up assessments, email reminders will be sent to incentivise follow-up completion. Reminder emails will be sent at weekly intervals, until the follow-up assessments are completed or until the maximum number of reminders (i.e., three) has been sent, whichever comes first.

### Training tasks

***Affective control training.*** The three versions of the AffeCT tasks are described below and depicted in
Figure 2.

**Figure 2. f2:**
[figure not shown]
Affective control training tasks. The figure depicts sample trials for each of the three training tasks:
**A**) visuospatial
*n*-back,
**B**) auditory
*n* –back, and
**C**) dual
*n*-back task. Trials depicted with a light blue background require a “No Match” button press, whereas yellow backgrounds indicate “Match” (i.e., target) trials in the respective modality. The green border provides feedback to participants, where green indicates the response was correct, whereas a red border appears for incorrect trials. Feedback is provided after each response or when a trial times out. The example block in
Figure 2 is depicted for
*n* = 1. Match trials for the visuospatial
*n*-back training task are trials where the current face is presented in the same location as the face
*n* positions back. For auditory
*n*-back match trials, the same word is presented as the one
*n* trials back. The dual
*n*-back training task includes both modalities and both types of target trials (for additional buttons appearing on screen with the dual
*n*-back see the task description below). 2500ms = the maximal (duration is self-paced up to 2500ms) time between onset of one stimulus and the next (i.e., total trial time); 500ms = face presentation time; 150ms = feedback presentation time; 500-950ms = word presentation time. 20 +
*n* = each block consists of 20 +
*n* trials.

***Training progression.*** The first three days will start at
*n* = 1. From day 4 onward participants will select one of the versions to train on and training will start at the average level of
*n*-back achieved on the previous training session with the selected version. During each individual training session, the difficulty level will be titrated to each participant’s maximum capacity with
*n* increasing by 1 if performance reaches ≥ 70% accuracy and decreasing by 1 when accuracy is ≤ 30%. Accuracy feedback will be provided after each response. A red boarder will flash up around the grid for false alarms (participant presses Match on a non-target trial) or misses (participant presses No Match on a target trial or fails to provide any response). A green boarder will flash up for all correctly classified trials.

***Stimuli.*** Each of the training versions will include 20% neutral stimuli and 80% affective stimuli to train the flexible engagement and disengagement from affective information. 30% of the trials will constitute target trials. The words included in the dual and auditory versions of the AffeCT are derived from the Affective Norms for English Words database
^49^ and with the exception of the positive words were included in previous versions of this training task
^21,
35^. Positive stimuli are included in the current training task because of the salience of positive material in adolescence
^50^, as well as research showing a critical role of reward processing in the onset of mental health problems
^51,
52^. The words are 20% neutral, 30% positive and 50% negative.

The faces stimuli were selected from several different databases, which are licenced for use online, to provide a diverse stimulus set in terms of demographics and emotional expressions. The databases included are: the Chicago Face Database
^53^, the Radboud Faces Database
^54^, the London Face Research Set
^55^, the Emotional Faces Stimulus Set
^56^, and the NIMH Child Emotional Faces Picture Set
^57^. Our final stimulus set includes child, adolescent and adult faces of female and male gender. The ethnic appearances of the faces included are African, Asian, Caucasian, Latin American, Mediterranean, Middle Eastern, and Mixed Race. We denote the ethnicity here as appearance only as not all the actors’ origins were recorded across the different databases. The emotional expression of the faces included are happy, angry, fearful, sad, and neutral. In each training session 50% of the faces are female, 50% of the faces are from child and adolescent models. The affective expressions included in each training session are 20% neutral, 20% angry, 20% fearful, 20% sad (i.e., 60% negative), 20% happy.

***Visuospatial n-back.*** In the visuospatial
*n*-back task faces appear for 500 ms on a 4×4 grid. The task requires participants to indicate within 2.5 s whether the face they are seeing in the current trial is presented in the same location as the face presented
*n* trials back. Responses are provided via “No Match” or “Match” button press.

***Auditory n-back.*** In the auditory version of the training task participants are presented with words over headphones. On each trial they have 2.5 s to indicate via button press (see visuospatial
*n*-back), whether the word presented in the current trial is the same as they heard
*n* trials back.

***Dual n-back.*** The dual version of the task presents participants with the visuospatial and auditory
*n-*back simultaneously. The task requires participants to indicate whether the location in which the face is appearing on the current trial is the same as the location in which a face appeared
*n* trials back. At the same time, they indicate whether the word they are hearing on the current trial is the same as the word
*n*-trials back. The response options include four buttons: “No Match” for non-target trials, “Location Match”, for trials including only a visuospatial target, “Word Match”, for trials including only an auditory target, and “Both Match” for trials including both an auditory and visuospatial target. One third of the target trials are visuospatial targets, one third auditory targets, and one third dual targets.

***Placebo training.*** The P-Training task requires participants to indicate via button press (“Match”, “No Match”) whether two panels display exactly the same stimuli in the same positions on a grid. In the shapes version the stimuli are random geometric shapes. The faces and words versions include the same stimuli as the AffeCT. Each trial is self-timed up to a maximum of 90 s after which participants are asked to respond more quickly. The initial trial includes 5 items per panel, the number of items per panel increases with participant’s performance. 

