**Figure 4. f4:**
[figure not shown]
Predicted structure of affective and cognitive functioning at baseline. The figure offers a schematic representation of the predicted structure of cognitive and affective control in adolescents. Raven’s i1 – 12 = items 1 – 12 on the Raven’s Advanced Progressive Matrices; d’ = d prime on backward digit span; RT = reaction time; rE = proportion random errors; Acc = percentage trials correct. Rectangular boxes = measured variables; ovals = latent constructs.

To investigate the first hypothesis (
*affective control training hypothesis*) we will use mixed effects modelling with training group as fixed effect and time as within-subject effect. The outcome of interest will be
*d*’ achieved on the affective
*n*-back task. Additionally, we will explore the impact of training on reaction time as a secondary outcome of interest. For the secondary analyses to be considered significant, we will apply a Bonferroni correction to reduce the threshold for statistical significance for two comparisons (accuracy and reaction) to α ≤ .025. We will then explore whether any effects of group and time are moderated by total training time (mins), total number of individual training sessions and ratio of time spent training on training task C relative to A and B. We plan to include these overlapping measures separately as they arguably provide different types of information. Specifically, total training time will allow us to explore dose-response relationships. The other two measures, we propose, index more motivational factors such as diligence and/or motivation by the monetary incentive. To facilitate interpretation of any potential moderating effect, we will use a SEM trees approach to these moderators and enter the relevant groupings as moderators. We will additionally investigate the effect of time spent on each training version separately on the outcome of interest and compare the effect of time spent on the single versions versus time spent on the dual version.

Our second hypothesis (

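### With 30% targets, the 70% and 30% progression bounds coincide with constant responding, so the n-back is not titrated to capacity for participants biased towards 'No Match'

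*Protocol article*

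**What the plan says.** All references are to the Protocol article.

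- **Training progression** states the aim that "the difficulty level will be titrated to each participant’s maximum capacity". The same paragraph then gives the rule that moves the level between blocks: "increasing by 1 if performance reaches ≥ 70% accuracy and decreasing by 1 when accuracy is ≤ 30" per cent. From day 4, a session starts at the average level reached in the previous session on the chosen version.
- **Stimuli** fixes the target share: "30% of the trials will constitute target trials".
- **Scoring** is not formally defined for progression, but the feedback rules indicate it. "A green boarder will flash up for all correctly classified trials", and the red border marks false alarms and "misses (participant presses No Match on a target trial or fails to provide any response"). A 'No Match' press on a non-target therefore counts as correct.
- **The Figure 2 legend** gives the block length: "each block consists of 20" + n trials.
- **The Figure 4 legend** glosses accuracy as "Acc = percentage trials correct", though for the baseline structural model.
- **Response options** are two buttons in the visuospatial and auditory versions and four in the dual version.
- **Statistical analyses** takes d' on the affective n-back as the outcome for hypothesis 1. Total training minutes, number of sessions and the share of time on version C are moderators.

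**The concern.** An adaptive rule holds a person at the limit of capacity only if success at a level requires doing the task at that level. Here the upward bound equals the share of non-targets and the downward bound equals the share of targets. Someone who has stopped updating and falls back on the commoner answer can satisfy the upward bound, and the level then rises although nothing is being held in memory. The raised level also carries into later sessions.

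The issue is the dose of training actually delivered. Sessions count and are paid by duration, with a 10-minute minimum and no stated performance condition. Blocks of default responding therefore enter total training time and session count, two of the planned moderators, on the same footing as blocks of real training.

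**Working it through.** The plan states no derived figure to reproduce; 70%, 30% and 30% are design constants.

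**Inputs from the document.** Target share 0.30; up at ≥ 70%; down at ≤ 30%; block length 20 + n; two response buttons (versions A and B) or four (version C).

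**Assumptions.** Accuracy is the percentage of trials correct and is applied per block. The first n trials have no item n back, so steps 2 to 4 use 20 scored trials with 0.30 × 20 = 6 targets and 14 non-targets. The level then rises at 14 or more correct and falls at 6 or fewer.

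**Step 1: constant responding.**
- Always 'No Match': 1 − 0.30 = 70%, which meets the upward bound.
- Always 'Match': 30%, which meets the downward bound.
- In the dual version the targets are split in thirds (10% location, 10% word, 10% both), so 'No Match' is again right on 70% of trials.

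**Step 2: block level.** Always 'No Match' gives 14/20 = 70%, so n rises after every block.

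**Step 3: weak responders, two-button versions.** Number correct = Bin(14, correct-rejection rate) + Bin(6, hit rate).

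| Responder | Correct rejections | Hits | P(up) | P(down) |
|---|---|---|---|---|
| d' = 0.5, false alarms 10% | 0.90 | Φ(0.5 − 1.28) = 0.22 | 0.62 | 0.000004 |
| d' = 0.5, unbiased criterion | Φ(0.25) = 0.60 | 0.60 | 0.25 | 0.007 |
| 95% correct rejections, 20% hits | 0.95 | 0.20 | 0.80 | about 0 |
| Random pressing | 0.50 | 0.50 | 0.058 | 0.058 |

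The first two rows have the same sensitivity. Response bias alone moves the promotion rate from 25% to 62%.

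**Step 4: random pressing, dual version.** With four buttons each trial is correct with probability 0.25. Bin(20, 0.25) gives P(≤ 6) = 0.79 and P(≥ 14) = 0.00003.

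**Step 5: dependence on the target count.** If all 20 + n trials are scored, the constant 'No Match' responder obtains:
- fixed 6 targets: 15/21 = 71.4% at n = 1, rising with n (22/28 = 78.6% at n = 8), so up every block;
- 30% of 20 + n rounded down: never below 70%, so up every block;
- rounded to nearest: 15/21 = 71.4% at n = 1, then 7 targets in 22 trials, 15/22 = 68.2%, so it stalls at n = 2;
- rounded up: 7 targets in 21 trials, 14/21 = 66.7%, so it never leaves n = 1.

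If targets are instead drawn at random on each of 20 scored trials, Bin(20, 0.7) gives P(up) = 0.61 and P(down) = 0.0003 per block, so n still climbs.

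**The case against.** The best reply is that accuracy is not defined for the progression rule. The article is condensed and refers to additional methods in a supplement not at hand. An index such as d' or hits minus false alarms would remove the problem. That is possible, and it is why the point is conditional; but the text available scores every correctly classified trial and mentions no minimum hit rate.

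Several stronger readings are tempting and are not supported:

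- *The rule fails for everyone.* It does not. An engaged participant is still moved upward, and the conflict bites on those who lean towards 'No Match'.
- *A constant responder necessarily reaches a very high n.* This needs a fixed 6 targets, rounding down or random draws. Other roundings stop the climb at n = 1 or n = 2.
- *Chance performance inflates the level.* In the two-button versions random pressing moves up as rarely as down. In the dual version, on which participants are told to concentrate, it usually moves down.
- *Hypothesis 1 is compromised.* The benchmark is otherwise identical to the visuospatial training task, so as written the same rule may set the n at which it is performed. But d' is sensitive to this bias, and constant responding shows no discrimination.
- *A planned analysis relies on the level reached.* None does. Payment does not depend on level either, so the rule creates no incentive to game it.

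**Conclusion.** The point stands in limited form. On the percentage-correct reading, both progression bounds equal the scores of strategies with no discrimination, and the claim of titration to maximum capacity does not hold for participants biased towards 'No Match'. With 6 targets in 20 scored trials, constant 'No Match' is promoted every block, and a weak biased responder in 62% of blocks with practically no demotion, against 25% for an unbiased responder of equal sensitivity.

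The size rests on the percentage-correct reading, on block-wise application and, for the constant responder, on how the target count is set. How many adolescents will respond this way cannot be judged from the document. What is affected is the training dose and its use as a moderator, not the validity of the d' comparison. It should be corrected, because a stated rule lacks the property claimed for it.

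**What to change.** 1. Reconcile three statements: the progression criterion (Training progression), the target share (Stimuli) and the claim of titration to maximum capacity. Which of them changes is for the investigators to decide.
2. State the performance index used for progression, the trials it is computed on, and how the target count is set in a block of 20 + n trials.
3. From the trial responses that the app already scores for feedback (assuming they are stored), identify training blocks with zero hits or d' ≤ 0. In a sensitivity analysis, exclude those blocks from training time and session count and see whether the moderator results change.

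**Cost.** Any change to the app needs a retest and an amendment. Trial status reports that 64 participants (64/200 = 32% of the target) have had the pre-training assessment. None has completed training, but some may have started. The benchmark n-back should therefore stay the same at T1 and T2, so that the hypothesis 1 comparison remains like with like. If the training task changes, the benchmark will no longer match it exactly, and the protocol should say so. Item 3 needs no new data collection if responses are stored.

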### Pre- and post-training session assessments

For an overview of all measures that will be included in T1-T4 see
Figure 3.

**Figure 3. f3:**
[figure not shown]
Schedule of enrolment, interventions and assessments (SPIRIT). SPIRIT = Standard Protocol Items: Recommendations for Interventional Trials. T1 = pre-training assessment; T2 = post-training assessment; T3 = 1-month follow-up assessment; T4 = 1-year follow-up assessment.

***Demographics.*** Self-identified gender, ethnicity and parental education level will be assessed. Parental education will be included as a proxy measure for socioeconomic status (SES). Parental education has been shown to be a robust indicator of SES
^58^ and has been previously used by our group in similar samples (e.g.,
59).

***Pubertal development.*** Pubertal development will be assessed with the well-validated, self-report Pubertal Development Scale
^60^. The scale will be sent to participants via email link, so that they can complete it in private at home.

***Self-reported mood and mental health.*** All self-report measures will be administered on a computer screen.

*Positive and negative affect.* To assess current positive and negative affect participants will complete the state version of the Positive and Negative Affect Schedule
^61^. The scale requires individuals to rate the extent to which 10 positive and 10 negative adjectives describe them. We will ask participants to rate the adjectives with respect to how well they describe them over the past week.

*Mental health difficulties.* Mental health problems will be assessed with the Strengths and Difficulties questionnaire. The questionnaire is a 25-item self-report measure, which is divided into five subscales
^62,
63^. Four of the subscales measure difficulties and one subscale measures a strength, prosocial behaviour. The difficulties subscales assess emotional symptoms (internalizing symptoms), conduct problems, hyperactivity/inattention and peer relationship problems. The measure has been shown to have good psychometric properties in the age group that will be recruited for the current study (Cronbach’s
*α* of 0.80), as well as good sensitivity, specificity and prospective utility
^64–
66^.

*Emotion regulation.* The 36-item Difficulties in Emotion Regulation Scale (DERS) will be administered to assess emotion regulation
^67^. The DERS has six subscales that measure:
*non-acceptance*, the propensity to experience secondary negative emotions in response to negative emotions;
*goals*, difficulties engaging with goal-directed behaviours when upset;
*impulse*, the ability to control one’s behaviour when experiencing negative emotions;
*awareness*, the tendency to attend to emotions;
*strategies,* individuals’ perception that emotions cannot be controlled; and
*clarity*; individuals’ ability to correctly identify their emotions
^67^. The scale has shown high internal consistency, Cronbach’s
*α* = 0.93
^67^ and has been reliably used in the age range included in the current study
^68^.

*Self-regulation.* The Brief Version
^69^ of the Self-Control Scale
^70^ will be administered to measure self-regulation. The scale has 13 items and has shown good internal consistency
^69,
71^, 

***Cognitive-affective task performance.*** Three tasks will be included to assess the impact of AffeCT relative to P-Training on the different facets of affective control: inhibition, updating and set-shifting.

*Inhibition.* Inhibition of affective interference will be assessed using an affective Stroop task
^41^. In this modified version of the task participants indicate whether adjectives are happy or sad. The words are superimposed on the image of a face, resulting in three trial types: congruent (emotions of the word and face are matched), incongruent (emotions of the word and face are mismatched) or neutral (the word is superimposed on scrambled face image). This modified version of the task includes only happy and sad as emotion categories, whereas the original task also included words and faces expressing anger. The current version also includes only four words per emotion category and the faces are from two adult actors and two child/adolescent actors (50% female). These modifications were made to adapt the difficulty level of the task for younger participants and to make the stimuli age-appropriate. The face stimuli are derived from the same face databases as the training stimuli.

Feedback is provided after each trial with a red or green border appearing around the image for 200 ms, indicating an error or correct response, respectively. Trials are self-paced up to 4 s. If no response is detected a red border appears and the next trial is presented. There are 96 trials in total with each actor being paired with each of the eight adjectives in each condition.

*Shifting.* The capacity to shift flexibly between task-demands will be assessed using an affective set-shifting task. The task is an affective version of the Madrid Card Sorting Task
^72^. Participants are dealt a card, which they are asked to assign to one of four decks according to three possible sorting rules: card color, number of items and shape (neutral version) or emotional expression (affective version). Sorting rule switch randomly after 6 to 9 trials (on average after 8 trials). Each rule is presented twice in the neutral and affective versions each, resulting in 96 trials. Participants are required to respond within 30 s, after which the trials are recorded as an error. The presentation order of the affective and neutral versions is randomized. Performance on the task is operationalized as random errors. These are errors that occur on any trial in the series after the initial two trials (needed to establish the correct sorting rule). Random errors are most reliably associated with mental health outcomes in adolescents on this version of the task
^12^.

*Updating.* Updating will be assessed with an affective backward digit span task, where participants are presented with digits (1500 ms) in serial order. The task starts with two digits per trial. Following the final digit in each trial, a keypad appears and participants are required to enter the digits in reverse order. Each span level is presented twice on this task. At least one out of two correct trials per span level is needed for progression to the next level. If both trials are incorrect the task is terminated. To manipulate valence, the digits are presented over negative and neutral background images. The images are from the Geneva Affective Picture Database
^73^.

*Fluid intelligence.* The 12-item version of the Raven’s Advanced Progressive Matrices will be used to assess intelligence
^74^. Participants will be told that they should complete the task as quickly as possible. The measure has good psychometric properties
^75^. We chose the Raven’s Advanced Progressive Matrices because it is sensitive in the wide age range included in the current study.

***Benchmark training tasks.*** The benchmark versions of the training tasks will be identical to the training versions with a few exceptions noted below.

*Visuospatial n-back tasks*. The benchmark version of AffeCT is identical to the visuospatial
*n*-back that will be used in the AffeCT with the exception that in the benchmarking version of the task only four blocks will be presented. Two of the blocks will include faces and two blocks will include scrambled faces.

*Placebo task*. For the benchmark version of the P-Training we will present the faces version of the feature match task. The version is identical to the training version with the exception that it is only 90 s long.

